## Abstract

**Background:**

Spinal cord injury (SCI) frequently disrupts the autonomic nervous system (ANS), impairing cardiovascular function and affecting cerebrovascular and cognitive functions. While high-intensity interval exercise (HIIE) is known to improve cardiovascular and cognitive functions in non-injured populations, its impact on these functions in individuals with SCI, especially those with high-level injuries, is not well-documented.

**Objective:**

The primary aim of this study is to investigate the acute effects of a single bout of HIIE on ANS related-cardiovascular (ANS-CV) function in individuals with chronic SCI at or above T6. The secondary aims are to examine the acute effects of the same HIIE bout on cerebrovascular dynamics and cognitive performance in this population.

**Methods:**

In this prospective case-control study, 15 individuals with SCI at T6 or above and 15 age- and sex-matched uninjured controls will be assessed. Measures include heart rate, heart rate variability, blood pressure, systolic blood pressure variability, cerebral blood flow velocities, and cognitive performance, analyzed pre- and post-HIIE. The sit-up test and face-cooling test will be used to activate the ANS-CV system. Post-exercise assessments will begin 5 minutes after completing the HIIE session. Cardiovascular testing will be conducted first and is expected to last 36 minutes. Cerebrovascular and cognitive testing will follow, starting approximately 41 minutes after the HIIE session. Covariates such as physical activity levels, pre-morbid intelligence, and psychological distress will be considered. This study has been approved by the University at Buffalo Institutional Review Board (IRB) (Approval Number: MOD00013354) and registered on ClinicalTrials.gov (Registration Number: NCT06274658).

**Results:**

We hypothesize that HIIE will improve cardiovascular and cerebrovascular functions and enhance cognitive performance in the SCI group. Data will be analyzed using linear mixed-effects models to evaluate the interaction effects of group and exercise.

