We designed a rigorous prospective case-control study that includes a non-injured control group to bridge the knowledge gap regarding the impact of HIIE on ANS-CV, cerebrovascular, and cognitive functions in individuals with a NLI at or above T6. For this study, we selected arm cycling based on prior evidence of its acute benefits for ANS-CV function in SCI [26]. High-intensity exercise was defined as a rating of perceived exertion (RPE) ≥14 (Borg 6–20 scale) per ACSM guidelines [39]. Although ACSM also classifies intensity using HR (≥70% HR_max_), we prioritized RPE due to ANS dysfunction in SCI at or above T6, which may attenuate HR responses to exercises [36]. The primary aim is to evaluate the effects of a single bout of HIIE on ANS-CV function in individuals with a chronic SCI at or above T6. Secondary aims include assessing the impact of HIIE on cerebrovascular dynamics and cognitive performance in SCI. We hypothesize that an acute HIIE session will improve ANS-CV, cerebrovascular, and cognitive functions in SCI, but these benefits will be attenuated compared to non-injured controls due to ANS dysfunction. To account for individual variability, covariates such as physical activity level, pre-morbid intelligence, and psychological distress will be considered in the analysis.

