## Methodology

### Study design

This is a case-control study that includes a group of individuals with SCI and a sex- and age-matched uninjured control group to examine the effects of injury on exercise responses. The study protocol includes one initial visit for consent and maximal exercise testing (Visit 1) and one experimental visit (Visit 2) during which participants are exposed to a single session of HIIE. Fig 1 illustrates the schedule of enrollment, assessment, and intervention for the study (Fig 1).

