### Sample size calculation

A pilot study was conducted to guide the design of this research. Based on the pilot data, we plan to recruit up to 20 participants per group, accounting for an estimated 20% attrition rate [40], to ensure at least 15 participants with complete data to be included in the analyses for sufficient statistical power (β ≥ 80%, α = 0.05). This sample size is calculated based on using a two-sample two-sided t-test to detect significant differences between the SCI and control groups for the change from baseline in ANS-CV function. High-frequency heart rate variability (HF HRV) reflects parasympathetic activity, with normalized units accounting for changes in total power during autonomic activation [41–43]. Similarly, low-frequency systolic blood pressure variability (LF SBPV; Mayer waves) serves as a biomarker of sympathetic vasomotor control [44]. Based on the pilot study, the estimated minimum detectable effect sizes are 24.97 for the difference in normalized HF HRV and 3.52 mmHg² for the difference in LF SBPV between groups, which are the two primary ANS-CV variables.

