### Data analysis

To analyze the impact of HIIE on cardiovascular, cerebrovascular, and cognitive functions in individuals with SCI compared to controls, linear mixed-effects models (LMMs) will be utilized. These models will assess the main effects and interactions of group (SCI vs. controls) and time (pre-HIIE vs. post-HIIE) across different outcomes, with specific adjustments tailored to the type of function being analyzed. The general model can be structured as follows:

Y_ij_ = β_0 _+ b_i_ + β_1_Group_i_ + β_2_Time_j _+ β_3_Group_i _× Time_j _+ β4 × Covariates_i _+ ∊_ij_

Where:

Y_ij_ represents the dependent variable (e.g., HR, BP, HF HRV, LF SBPV, BRS) for subject *i* at time j (j = 0,1).Group_i_ is the SCI/control status for subject *i* (SCI: Group_i _= 1, Control: Group_i_ = 0).Time_j_ is the *jth* time point (pre-HIIE: Time_j_ = 0, post-HIIE: Time_j_ = 1).Covariates_i_ are additional covariate(s) for subject *i*. For dependent variables within cardiovascular and cerebrovascular functions: baseline physical activity levels. For cognitive function: pre-morbid intelligence and psychological distress.b_i_ is the random effect for subject *i* to account for within-subject correlation over time and is assumed independent N(0, σ_b_^2^).∊_ij_ is the residual error term assumed independent N(0, σ_∊_^2^).

Estimation of parameters will be analyzed by restricted maximum likelihood estimation (REML). Wald tests will be used to assess the significance of the predictors, with the significance level set at p < 0.05. All analyses will be conducted using RStudio (© 2009–2024 Posit Software, PBC).

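### Every participant exercises at the only experimental visit, so the change within SCI cannot be attributed to HIIE alone; Group × Time is protected only against session change that both groups share

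*Protocol article*

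**What the plan says.** - **Design.** Study design provides for "one experimental visit (Visit 2) during which participants are exposed to a single session of HIIE". Experimental procedure applies the HIIE to all participants, and no rest or sham session is described. The uninjured group is there to show how injury alters the response to exercise.
- **Aim.** The primary aim (Abstract, Objective; Introduction, last paragraph) is the effect of one HIIE bout on autonomic cardiovascular function in people with SCI. The Introduction adds: "We hypothesize that an acute HIIE session will improve ANS-CV, cerebrovascular, and cognitive functions in SCI", with smaller benefits expected than in controls.
- **Model.** Data analysis names main effects and "interactions of group (SCI vs. controls) and time (pre-HIIE vs. post-HIIE) across different outcomes", coded SCI = 1, control = 0, pre = 0, post = 1. The Abstract describes the interaction differently: "Data will be analyzed using linear mixed-effects models to evaluate the interaction effects of group and exercise".
- **Sample size.** It rests on "using a two-sample two-sided t-test to detect significant differences between the SCI and control groups for the change from baseline in ANS-CV function".
- **Reading rule.** The Discussion says that SCI responses similar in direction and pattern to those of controls may point to adaptive or beneficial change, even if they are smaller.
- **Disclosure.** The Discussion concedes that the study cannot set definitive efficacy endpoints or minimum clinically important differences. Limitations lists seven items; the absence of a no-exercise condition is not one of them.

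**The concern.** Nobody contributes data without exercise, so exercise never varies separately from whatever else differs between the two test blocks. The schedule builds in several such differences:

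- The face-cooling and sit-up tests are repeated within the visit.
- Cognitive tests come before the cardiovascular battery at baseline and after it post-HIIE. Post-HIIE cognition is therefore measured soon after a cold and an orthostatic challenge; baseline cognition is not.
- Alternate forms are planned for three cognitive tests. The Stroop test is not among them, and nothing comparable is described for the primary autonomic outcomes.

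At stake is the causal conclusion. A pre-to-post change in SCI could be taken as an effect of HIIE, and a change common to both groups could be taken as possible benefit, when the design separates neither from a session effect.

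**Working it through.** **1. Inputs.** 15 analysed per group (Abstract, Methods; Sample size calculation); two-sided α = 0.05; power at least 80%; detectable differences 24.97 n.u. (HF HRV) and 3.52 mmHg² (LF SBPV). The article gives no SD of change and no size for a change unrelated to exercise.

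**2. The plan's own figure.** Without an SD, 15 per group can only be solved backwards. For a two-sample t-test with 28 df, 80% power needs a standardised difference of 1.06. The implied SDs of change are 24.97/1.06 = 23.6 n.u. and 3.52/1.06 = 3.32 mmHg². Recruitment is consistent with the stated attrition: 15/0.8 = 18.75, so 19, against up to 20 planned. Nothing is wrong here; the SDs serve only as a scale below.

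**3. What each contrast estimates.** Let h be the true HIIE effect and s the session change from all other causes, with subscript 1 for SCI and 0 for controls.

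| Contrast | Coefficient | Expected value |
|---|---|---|
| Change in controls | β2 | h0 + s0 |
| Change in SCI | β2 + β3 | h1 + s1 |
| Group × Time | β3 | (h1 − h0) + (s1 − s0) |

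Nothing removes s1 from the SCI change. In β3 the session terms cancel when s1 = s0.

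**4. Rejection rates with h1 = h0 = 0.** With two complete time points, a random intercept and covariates fixed over time, the model contrasts equal change-score contrasts. With pooled variance (28 df) and drift d in SDs of the change score:

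- within SCI: noncentrality = d√15, i.e. 0.97 at d = 0.25 and 1.94 at d = 0.5;
- Group × Time, for a group difference in drift of d: noncentrality = d√(15/2), i.e. 0.68 and 1.37.

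| Assumed drift d | HF HRV (d × 23.6) | LF SBPV (d × 3.32) | Within SCI | Group × Time, same drift in both groups | Group × Time, drift in SCI only |
|---|---|---|---|---|---|
| 0 | 0 | 0 | 5% | 5% | 5% |
| 0.25 | 5.9 n.u. | 0.83 mmHg² | 15.5% | 5% | 10.1% |
| 0.5 | 11.8 n.u. | 1.66 mmHg² | 46.4% | 5% | 26.2% |
| 1.0 | 23.6 n.u. | 3.32 mmHg² | 96.2% | 5% | 75.3% |

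A simulation of 40,000 trials per scenario agreed. At d = 0.5 it gave 46% within SCI, 4.9% for Group × Time with shared drift and 25.7% with drift in SCI only. If the planned Wald tests use a normal reference, the null rate is about 6% instead of 5%, and shared drift still leaves Group × Time unchanged.

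**5. Timing.** The cardiovascular battery lasts 15 + 1 + 5 + 15 = 36 min. With 10 min of HIIE and 5 min of recovery, each test recurs about 36 + 10 + 5 = 51 min after its first run. Post-HIIE cognitive testing starts at about 5 + 36 = 41 min.

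**6. The Discussion's reading rule.** If h1 = h0 = 0 and s1 = s0 = s ≠ 0, both groups change in the same direction by the same amount. That is the pattern the Discussion would regard as possibly beneficial, with no HIIE effect present.

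**The case against.** A reader might infer that all the planned tests, including the interaction, reject for any session-related change. The documents do not support that. The interaction is the contrast named in the Abstract and the one behind the sample size. Drift of equal size in both groups leaves it at its nominal level, so the controls give real, if partial, protection.

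Other points on the plan's side also stand:

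- Data analysis labels the factor correctly as time; the group-and-exercise label appears only in the Abstract.
- No section states a null hypothesis of no HIIE effect. The claims of improvement are hypotheses, not conclusions.
- The Discussion speaks of comparing pre-to-post changes between groups and hedges what a similar pattern means.
- The drift sizes are assumptions, and the larger rejection rates belong to the within-SCI change, not to the interaction.
- The pre-post design is stated openly.

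This narrows the point but does not remove it. The primary aim concerns the effect within SCI, which is β2 + β3, and nothing cancels there. Drift that differs between groups is also plausible: the Introduction describes impaired blood pressure and heart rate regulation in this population, and the repeated tests challenge exactly that.

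**Conclusion.** The point holds in two parts. First, the pre-to-post change within SCI cannot be attributed to HIIE alone, because every participant exercises and no condition without exercise exists; this follows from the design and needs no assumption. Second, Group × Time is biased only by session change that differs between SCI and controls.

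The size is conditional on the assumed drift. At 0.25 to 0.5 SD with no HIIE effect, a within-SCI test rejects about 15% to 46% of the time. Group × Time rejects about 10% to 26% if the groups differ in drift by that much, and 5% if they do not. These rates assume 15 complete pairs per group, equal variances and a t reference with 28 df. They illustrate sensitivity and do not estimate how much drift will occur. The Discussion's rule on similar patterns is exposed, since shared drift produces that pattern.

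**What to change.** Change the wording as follows:

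- **Abstract, Results:** call the interaction group by time.
- **Abstract (Objective, Results), Introduction (last paragraph) and the opening of Data analysis:** describe the estimands as the pre-to-post change over the HIIE session within SCI (β2 + β3) and the group difference in that change (β3).
- **Discussion:** do not read a change shared by both groups as evidence of benefit from HIIE.
- **Limitations:** state that, without a no-exercise condition, changes cannot be attributed to HIIE alone, and name elapsed time, repeated provocation tests and the reversed test order as alternatives.

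No visits, participants, models or tests are added, so this is feasible with data collection under way. The cost is a less favourable claim.

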**Conclusions:**

This study is expected to fill the knowledge gap regarding the impact of HIIE on cardiovascular, cerebrovascular and cognitive functions in individuals with SCI at or above T6. The findings will provide crucial insights into immediate physiological responses while establishing foundational evidence for developing targeted, long-term exercise interventions to improve health outcomes in this population.

## Introduction

Spinal cord injury (SCI) frequently disrupts the autonomic nervous system (ANS), leading to impairments in cardiovascular [1], cerebrovascular [2], and cognitive [3] functions. Individuals with a neurological level of injury (NLI) at or above the 6th thoracic vertebra (T6) are particularly vulnerable to more severe ANS-related cardiovascular (ANS-CV) disruptions [4]. While most anatomical studies localize cardiac sympathetic preganglionic neurons to the T1-T4/5 spinal segments [5,6], some evidence suggests occasional extensions to T6 [7,8]. This anatomical distribution aligns with observations that a SCI at or above T6 results in significant ANS-CV dysfunction [4], often manifesting as impaired blood pressure (BP) and heart rate (HR) regulation, including orthostatic hypotension (OH) and autonomic dysreflexia (AD) [9,10]. Physical inactivity following SCI may exacerbate ANS-CV dysfunction, underscoring the critical role of sustained activity in preserving ANS-CV function [11,12]. The downstream cognitive consequences of ANS-CV dysfunction are further complicated by interacting psychosocial factors. Cerebral blood flow (CBF) dysregulation may impair cognitive performance [13], but this relationship is nuanced by pre-morbid intelligence and psychological distress, which may independently influence cognitive outcomes [14–16]. Thus, a comprehensive assessment of ANS-CV, cerebrovascular and cognitive functions in SCI should account for physical activity level, psychological distress, and pre-morbid intelligence.

Given the potential interplay among ANS-CV, cerebrovascular, and cognitive dysfunction in individuals with SCI [13], interventions targeting improvements in ANS-CV function may also yield benefits for cerebrovascular and cognitive outcomes in this population. While it has been well established that exercise positively impacts ANS-CV, cerebrovascular and cognitive functions in non-injured populations [17–19], critical gaps persist in the SCI literature. Current exercise guidelines for SCI focus primarily on cardiometabolic and respiratory outcomes, with limited evidence regarding their effects on ANS-CV, cerebrovascular, and cognitive functions [20]. Specifically, only 8 studies have quantified exercise effects on direct ANS-CV parameters (e.g., baroreflex sensitivity [BRS], HR and BP variabilities) [12,21–27], and even fewer have examined cerebrovascular [28] or cognitive outcomes [28–30]. Importantly, these studies often employed inconsistent exercise intensity protocols and included heterogeneous participants (e.g., varying NLI) [12,21–30], making it particularly difficult to draw definitive conclusions about individuals with a NLI at or above T6. For example, a 6-month whole-body exercise program using hybrid functional electrical stimulation rowing led to improved BRS in individuals with a NLI at T1 to T10 [21]. However, only three out of the forty participants met the target HR [22], which raises uncertainty about the intensity applied or potentially reflecting individual variations in physiological capacity to increase HR. More recently, Ozturk and colleagues showed increased CBF velocity (CBFV) in SCI, which is a biomarker of cerebrovascular function, during cognitive tasks following long-term exercise training [28]. However, this study primarily addressed the duration of each exercise session rather than its intensity, making it challenging to develop detailed exercise guidelines.

Emerging evidence demonstrates that high-intensity-interval exercise (HIIE) offers superior cardiovascular, cerebrovascular and cognitive benefits compared to moderate-intensity continuous training in the general population [31–34]. Additionally, recent work in SCI specifically shows that moderate-to-high intensity arm cycling [12,26,27], but not low-intensity exercise [25], improves ANS-CV function, suggesting that adequate intensity is critical for physiological adaptation in this population. HIIE has emerged as a promising intervention for individuals with SCI, with prior studies demonstrating its feasibility and benefits for cardiorespiratory fitness in this population [35]. The time-efficient nature of HIIE directly addresses a key barrier to physical activity, while its intermittent structure may enhance adherence through greater enjoyment compared to continuous training [35]. While these studies have established the practical advantages of HIIE, its effects on ANS-CV, cerebrovascular, and cognitive functions remain unexplored. It is important to note that ANS dysfunction in people with a NLI at or above T6 might attenuate these benefits, as impaired sympathetic outflow blunts cardiovascular responses during exercise [36,37] and compromises cerebrovascular adaptation [38]. Further, impaired muscle and respiratory function in SCI may reduce physical fitness benefits such as maximal oxygen consumption [21], subsequently limiting hemodynamic and cerebrovascular adaptations to exercise [28]. Therefore, using exercise methods that accommodate preserved motor function in this population, along with inclusion of non-injured controls in studies, will allow direct comparison of HIIE effects in an intact versus ANS compromised cohort to help clarify how SCI influences adaptation to exercise.

We designed a rigorous prospective case-control study that includes a non-injured control group to bridge the knowledge gap regarding the impact of HIIE on ANS-CV, cerebrovascular, and cognitive functions in individuals with a NLI at or above T6. For this study, we selected arm cycling based on prior evidence of its acute benefits for ANS-CV function in SCI [26]. High-intensity exercise was defined as a rating of perceived exertion (RPE) ≥14 (Borg 6–20 scale) per ACSM guidelines [39]. Although ACSM also classifies intensity using HR (≥70% HR_max_), we prioritized RPE due to ANS dysfunction in SCI at or above T6, which may attenuate HR responses to exercises [36]. The primary aim is to evaluate the effects of a single bout of HIIE on ANS-CV function in individuals with a chronic SCI at or above T6. Secondary aims include assessing the impact of HIIE on cerebrovascular dynamics and cognitive performance in SCI. We hypothesize that an acute HIIE session will improve ANS-CV, cerebrovascular, and cognitive functions in SCI, but these benefits will be attenuated compared to non-injured controls due to ANS dysfunction. To account for individual variability, covariates such as physical activity level, pre-morbid intelligence, and psychological distress will be considered in the analysis.

## Methodology

### Study design

This is a case-control study that includes a group of individuals with SCI and a sex- and age-matched uninjured control group to examine the effects of injury on exercise responses. The study protocol includes one initial visit for consent and maximal exercise testing (Visit 1) and one experimental visit (Visit 2) during which participants are exposed to a single session of HIIE. Fig 1 illustrates the schedule of enrollment, assessment, and intervention for the study (Fig 1).

**Fig 1 pone.0326861.g001:**
[figure not shown]
Schedule of Enrolment, Interventions, and Assessments. Notes: HIIE, high-intensity-interval exercise; TCD, transcranial Doppler; HR, heart rate; HF HRV, high frequency of heart rate variability; BP, blood pressure; LF SBPV, low frequency of systolic blood pressure variability; MCAv, middle cerebral artery blood flow velocity; PCAv, posterior cerebral artery blood flow velocity; CVLT-III, California Verbal Learning Test-Third Version, SDMT, Symbol Digit Modalities Test; COWAT, Controlled Oral Word Association Task.

This study has been approved by the University at Buffalo Institutional Review Board (IRB) on January 28, 2024 (Approval Number: MOD00013354) and registered on ClinicalTrials.gov (Registration Number: NCT06274658). The Principal Investigator (PI) will explain the study details to potential participants, and written informed consent will be obtained from all participants prior to their inclusion in the study.

### Sample size calculation

A pilot study was conducted to guide the design of this research. Based on the pilot data, we plan to recruit up to 20 participants per group, accounting for an estimated 20% attrition rate [40], to ensure at least 15 participants with complete data to be included in the analyses for sufficient statistical power (β ≥ 80%, α = 0.05). This sample size is calculated based on using a two-sample two-sided t-test to detect significant differences between the SCI and control groups for the change from baseline in ANS-CV function. High-frequency heart rate variability (HF HRV) reflects parasympathetic activity, with normalized units accounting for changes in total power during autonomic activation [41–43]. Similarly, low-frequency systolic blood pressure variability (LF SBPV; Mayer waves) serves as a biomarker of sympathetic vasomotor control [44]. Based on the pilot study, the estimated minimum detectable effect sizes are 24.97 for the difference in normalized HF HRV and 3.52 mmHg² for the difference in LF SBPV between groups, which are the two primary ANS-CV variables.

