## Discussion

High-intensity interval exercise (HIIE) as a therapeutic intervention for individuals with SCI has emerged as a promising area of research [35], particularly in its potential to address disruptions in ANS function [12,26]. While broader benefits of exercise for cardiovascular and cerebrovascular health are well-documented in the non-injured population [82,83], its specific effects on individuals with SCI, particularly those with a NLI at or above T6, remains poorly understood. Current evidence lacks normative values for ANS-CV and cerebrovascular parameters in SCI. While LF SBPV less than 2 mmHg^2^ predicts OH [44] and higher diastolic CBFV correlates with better cognitive performance [84], absolute thresholds defining ANS-CV or cerebrovascular dysfunction remain undefined for this population. While this acute cross-sectional study cannot determine definitive efficacy endpoints or minimum clinically important differences (MCIDs) for HIIE in SCI, the findings will identify acute physiological responses that may predict clinically meaningful outcomes. In particular, we will evaluate pre- to post-HIIE changes in the ANS-CV, cerebrovascular, and cognitive variables between the SCI and control groups. If the direction and pattern of post-HIIE responses in the SCI group resemble those observed in the control group, this may be indicative of adaptive or beneficial changes, even if absolute response magnitudes are blunted. Additionally, the outcome measures obtained from the control group may provide preliminary normative data to inform future investigations in this field. This is particularly relevant given the unique challenges faced for people with SCI, including impaired BP and HR regulation, and decreased cognitive performance, all of which can profoundly impact quality of life [13].

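### The primary aim is the HIIE effect within the SCI group, but the sample size and the planned tests address the change in controls and the between-group difference in change, not the SCI change itself

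*Protocol article*

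**What the plan says.** **Aim.** The abstract's Objective gives the primary aim in these words: "investigate the acute effects of a single bout of HIIE on ANS related-cardiovascular (ANS-CV) function in individuals with chronic SCI at or above T6". The Introduction repeats this as the primary aim.

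**Hypothesis.** It has two parts. The first is within SCI: "We hypothesize that an acute HIIE session will improve ANS-CV, cerebrovascular, and cognitive functions in SCI". The second is between groups: "these benefits will be attenuated compared to non-injured controls due to ANS dysfunction".

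**Sample size.** At least 15 analysable participants per group are planned, for 80% power at α = 0.05. The basis is a two-sided two-sample t-test "to detect significant differences between the SCI and control groups for the change from baseline in ANS-CV function". Both detectable effects given, 24.97 for normalized HF HRV and 3.52 mmHg² for LF SBPV, are differences between groups.

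**Analysis.** The Data analysis section fits a linear mixed model with Group, Time, Group × Time, covariates and a random subject intercept. It says: "These models will assess the main effects and interactions of group (SCI vs. controls) and time (pre-HIIE vs. post-HIIE". Control and pre-HIIE are coded 0; SCI and post-HIIE are coded 1. Inference is by Wald tests of the predictors at 0.05. The abstract's Results paragraph names the group-by-exercise interaction as what the models evaluate.

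**The concern.** The primary aim asks one question and the powered test answers another. Whether function changes after HIIE in people with SCI is a question about one group's change. Whether that change differs from the change in controls is a separate question, and the answer to one does not settle the other. If the plan is followed as printed, the main result for each primary variable will be an interaction p-value that is silent on the stated aim. The protocol also predicts improvement without saying which direction of change in HF HRV or LF SBPV counts as improvement.

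**Working it through.** **1. What each coefficient means under the stated coding**

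| | Pre (0) | Post (1) | Change |
|---|---|---|---|
| Control (0) | β0 | β0+β2 | β2 |
| SCI (1) | β0+β1 | β0+β1+β2+β3 | β2+β3 |

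β1 is the pre-HIIE group difference, and the covariates do not vary over time. Of the Wald-tested terms, only β2 and β3 carry an HIIE effect, and neither is the SCI change. If the main effect of time is read as an average over groups, it is β2+β3/2, which is still not the SCI change.

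**2. The plan's own figure**

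No SD of change is given, so 15 per group cannot be reproduced independently. It can be solved backwards. For a two-sample t-test with n = 15 per group, df = 28, noncentrality d√(n/2) and 80% power, d = 1.060. The implied SDs of change (assumed equal in both groups) are:

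- HF HRV: 24.97/1.060 = 23.56 n.u.
- LF SBPV: 3.52/1.060 = 3.32 mmHg²

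The attrition step is consistent: 15/0.80 = 18.75, so 19, within the planned maximum of 20.

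**3. Detectable SCI change at n = 15**

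For a paired t-test with df = 14, noncentrality d√n, two-sided 0.05 and 80% power, d = 0.778.

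- HF HRV: 0.778 × 23.56 = 18.3 n.u.
- LF SBPV: 0.778 × 3.32 = 2.58 mmHg²

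As a rough check, under a normal approximation the within-group figure is the between-group figure divided by √2: 24.97/1.414 = 17.7 and 3.52/1.414 = 2.49.

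**4. If the SDs differ**

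Hold the pooled variance fixed, (s_SCI² + s_C²)/2 = s².

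- Ratio 1:2: s_SCI = s√0.4, which is 14.90 n.u. or 2.10 mmHg². The detectable change is 11.6 n.u. or 1.6 mmHg².
- Ratio 2:1: s_SCI = s√1.6, which is 29.80 n.u. or 4.20 mmHg². The detectable change is 23.2 n.u. or 3.3 mmHg².

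**5. How the tests diverge**

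Share of 4,000 simulated trials with p < 0.05, for HF HRV with n = 15 per group and SD 23.56 in both groups:

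| True change, control / SCI | Control change | Interaction | SCI change |
|---|---|---|---|
| 24.97 / 0 | 97% | 80% | 5% |
| 24.97 / 24.97 | 96% | 5% | 97% |

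In the first row the group-averaged time effect is also significant in 80% of trials, although SCI did not change.

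**6. Under the protocol's own hypothesis**

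Fix control minus SCI change at D = 24.97, so that the interaction has 80% power, and let SCI change by a fraction r of the control change. Then control = D/(1−r) and SCI = r × control.

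| r | Control | SCI | Power for SCI change |
|---|---|---|---|
| 1/4 | 33.3 | 8.3 | 25% |
| 1/3 | 37.5 | 12.5 | 48% |
| 1/2 | 49.9 | 25.0 | 97% |

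So 80% power for β3 does not fix the power for the primary aim.

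**The case against.** **The design is comparative on purpose.** The Study design section says controls are there to show how injury affects exercise responses, and the Data analysis section sets SCI against controls. β3 is the right test of attenuation. This stands, and it narrows the point: the gap is in the primary aim and the first half of the hypothesis, not in the whole plan.

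**A contrast can be left to a statistical analysis plan.** The equation is offered as a general model, β2+β3 is estimable from it, and no analysis plan is at hand. This has some force for the missing contrast. It does not remove the mismatch between the stated aim and the stated power basis, both of which are printed in this document.

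**The SCI contrast is uncontrolled.** Both groups exercise and there is no no-exercise condition. The face-cooling and sit-up tests are repeated within one visit, so a pre-post change in SCI includes repeat-testing and time effects. β3 removes whatever part of these is common to both groups. This stands in full: β2+β3 should not be reported alone, and restating the aim is a legitimate alternative.

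**A stronger reading of the Discussion is tempting.** It says that if SCI responses in direction and pattern "resemble those observed in the control group, this may be indicative of adaptive or beneficial changes, even if absolute response magnitudes are blunted". A reader might infer that a non-significant interaction would be taken as support, or that any shared change would be counted as benefit. The text does not say so. It is hedged, follows a statement that the study cannot settle efficacy endpoints, and gives the interaction p-value no such role.

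**A reader might also infer that 15 is too few.** That is not shown. With equal SDs the SCI contrast detects a smaller change than the powered between-group test does.

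**Conclusion.** The point holds in this form: the stated primary aim is neither tested nor powered as written, while the attenuation half of the hypothesis is both. The coefficient argument depends only on the printed coding and needs no assumption. The figures are less firm. About 0.78 SD at n = 15 follows from the paired t-test, but its conversion to 18.3 n.u. and 2.58 mmHg² rests on SDs back-solved from the detectable differences and assumed equal in the two groups. Across SCI:control SD ratios from 1:2 to 2:1, which is itself an assumed range, the conversion runs from 11.6 to 23.2 n.u. and from 1.6 to 3.3 mmHg². The defect is more than missing detail, because the study's main conclusion turns on it. It does not call the design or the sample size into question.

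**What to change.** 1. Pre-specify β2+β3 (post minus pre in SCI) with its 95% CI, for HF HRV and LF SBPV, as the test of the stated primary aim. Keep β3 as the test of attenuation. Alternatively, restate the primary aim as the between-group difference in change, which is what is powered.
2. State in the Sample size calculation section that the 80% power applies to β3. Give the pilot SD of change in the SCI group and the SCI change detectable from it, in place of the back-solved figures above.
3. State for each variable which direction counts as improvement.
4. Report β2+β3 alongside β3, and say that without a no-exercise condition the SCI contrast includes repeat-testing and time effects.

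The cost is wording, one pilot SD per variable and one contrast per model. No new data, participants or procedures are needed. The change should be made before the data are analysed.
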